#### Feasibility

To evaluate the feasibility, successful production of tolDC after leukapheresis will be evaluated. This includes the production of sufficient numbers of tolDC and compliance of the final investigational product to the prespecified release criteria following cryopreservation.

### Secondary outcome measures

#### Clinical evaluation

The following clinical and laboratory assessments will be performed during a complete physical examination: vital signs, ECG, routine blood and urine samples, urine pregnancy test in female patients of reproductive potential and serological screening tests, according to the study schedule (figure 1 and table 4). Concurrent drug use or new AE will be reviewed and recorded.

EDSS is based on a standardised neurological examination and measures impairments in eight functional systems, including vision, brainstem, pyramidal, cerebellar, sensory, bowel and bladder, mental (cerebral) and ambulation. It has been used for over 20 years as a clinical outcome measure of MS disease progression and consists of a 10-point scale of disease severity ranging from 0, that is, no disability, to 10, that is, death from MS.^42^ All neurologists involved in patient evaluation will be EDSS training certified.

EDSS will be supplemented by three well-known, quantitative, continuous tests that evaluate ambulation (walking speed by the timed 25 foot walk test or T25FW, arm dexterity and function by the 9 Hole Peg Test or 9-HPT, and cognition by the Symbol Digit Modalities Test or SDMT).

The effect on disability progression will be characterised by reporting the proportion of patients who are free from disease progression. For this, disability will be assessed based on a sustained clinically relevant change seen in any one of the disability assessments: EDSS, T25FW, SDMT or the 9-HTP. Disease progression is defined by: 3-month sustained increase from baseline in the EDSS score (1 point in patients with baseline EDSS score 0 to 5.0; 0.5 point in patients with baseline EDSS score of 5.5–6.5) or 3-month sustained increase of at least 20% from baseline in the time taken to complete the T25FW or 3-month sustained increase of at least 20% from baseline in the time taken to complete the 9-HPT. Percent change from baseline after treatment in SDMT score will also be recorded.

#### MRI acquisition and evaluation

MRI is the current gold standard for non-clinical monitoring of MS, and MRI-derived markers have been established as standard outcome measures to monitor the treatment response in various MS clinical trials. MRI will be performed on the same 3T scanner throughout the study. The MRI protocol includes a 3PLANE scout, 3D T1-weighted image pregadolinium and postgadolinium (Dotarem, 20 mL) administration (voxel resolution 0.9×0.9×0.9, TR2300.0, TE2.29, TI 900.0) and a 3D FLAIR image (voxel resolution 0.4×0.4×0.9, TR5000.0, TE387.0, TI1800.0). The quantification of number of T2 lesions, T2 lesion load, number and volume of Gd-enhancing lesions, based on 3D FLAIR images and 3D T1-weighted images, is completely automatic avoiding inter-rater or intra-rater variability. The lesions are quantified within different brain regions. Disease activity or progression on MRI will be evaluated by pretreatment versus ongoing and post-treatment: (i) change in mean number of enhancing lesions; (ii) change in number of T1 Gd-enhancing and/or new or enlarging T2 lesions; (iii) percent change in T2 lesion load and (iv) percent change in brain volume. In order to compare MRI outcome measures from different studies, a standardised acquisition is guaranteed by (i) a uniform MRI protocol, (ii) the use of standard operating procedures for image acquisition and upload and (iii) training of local MRI operators and study coordinators for acquisition and upload.

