### Study population

#### Eligibility and enrolment

Patients with active relapsing-remitting and active progressive MS, diagnosed according to most recent McDonald criteria,^39 40^ and who are not eligible for or do not want to be treated with currently available DMT, will be recruited. Patients are included after written informed consent and enrolled in the study when the inclusion and exclusion criteria are met (table 2).

**Table 2 T2:** Inclusion and exclusion criteria. All the inclusion criteria must be fulfilled. The presence of any of the exclusion criteria shall exclude the patient

Inclusion criteria	Exclusion criteria
MS according to most recent McDonald criteria	Previous use of immunosuppressive or cytostatic treatment, including mitoxantrone, cladribine, alemtuzumab or bone marrow transplantation or stem cell transplantation at any time prior to enrolment
Age 18–60 years	Treatment with fingolimod or natalizumab or dimethylfumarate in the past 12 weeks or teriflunomide within the past 15 weeks or ocrelizumab/rituximab within the past 6 months prior to the first administration
EDSS of 0–6.5 inclusive	Pregnancy or planning pregnancy in the next 12 months and breast feeding
First signs or symptoms at least 3 months prior to enrolment in the study	Drug or alcohol abuse
Active MS (relapsing and/or progressive): one relapse in the past year and/or at least one enhancing lesion on brain MRI in the past year; at least one new or enlarging T2 lesion in comparison with a reference scan from maximum 1 year before	Inability to undergo MRI assessments
Normal peripheral B-cell count after treatment with ocrelizumab	
No evidence of relapse for at least 30 days prior to start of screening and throughout during the screening phase	History of or actual signs of immunodeficiency or malignancies
Positive T cell reactivity response to a mix of seven myelin-derived peptides	Concurrent clinically relevant cardiac, immunological, pulmonary, neurological, renal or other major disease
Able to sign informed consent and comply with the protocol assessments	Active or chronic infection (hepatitis B or C, HIV, syphilis or tuberculosis)
No wish to be treated with currently available DMT	Splenectomy
Appropriate venous access and *adequate cervical lymph nodes on ultrasound mapping	

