**Figure 1 F1:**
[figure not shown]
Study design. Treatment will start at V_1_, approximately 4 weeks after the leukapheresis. Patients will receive additionalinjections on week +2 (V_2_), week +4 (V_3_), week +6 (V_4_), week +10 (V_5_) and week +14 (V_6_). Patients will have follow up visits one month, and 3, 6 and 12 months following the last study treatment.

**Table 4 T4:** Study calendar. The different visits, examinations, tests and the tolDC administration are detailed on the tabular study schedule overview.

	Screening		Treatment period							Safety follow-up			
	Ts	Baseline (T0)	V1	V1 +1 day	V2	V3	V4	V5	V6	F1	F3	F6	F12
Informed consent	·												
Inclusion and exclusion criteria	·												
IFN-γ EliSPOT (T cell reactivity assay)	·		·				·+1w		·+1w		·		
Leukapheresis		·											
TolDC preparation		·											
TolDC treatment			·		·	·	·	·	·				
Patient evaluation:													
Vital signs (HR, BP, …)	·	·	·		·	·	·	·	·	·	·	·	·
ECG	·	·	·		·	·	·	·	·	·	·	·	·
Blood analysis for safety (1×5 mL EDTA tube and 2×10 mL serum tubes)	·	·	·		·	·	·	·	·	·	·	·	·
Urine pregnancy test	·	·	·		·	·	·	·	·	·	·	·	·
Full neurological examination (EDSS, 9-HPT, T25FW, SDMT, MSQOL-54)	·		·										
Pain score after treatment injection			·		·	·	·	·	·				
MRI	·	·	·		·		·+1w	·+1w	·+1w		·	·	·
Immunomonitoring (10×10 mL heparin tubes+1 serum tube)			·				·+1w		·+1w		·		
Biobanking for follow-up immunomonitoring													
(Serious) Adverse events and concomitant medication	Continuous												

BP, Blood Pressure; ECG, Electrocardiogram; EDSS, Expanded Disability Status Scale; 9-HPT, 9 Hole Peg Test; MRI, Magnetic Resonance Imaging; MSQOL-54, Multiple Sclerosis Quality of Life-54; SDMT, Symbol Digit Modalities Test; T25FW, Timed 25 Foot Walk; tolDC, tolerogenic dendritic cells.

In Belgium (MS-tolDC), tolDC vaccination occurs through intradermal injection at five alternating sites (100 µL/site) in the posterior neck region to ensure lymphatic drainage to superficial and deep cervical lymph nodes (5–10 cm from the cervical lymph nodes). In addition, in Spain (TOLERVIT-MS), an expert physician will inject tolDC directly in the cervical lymph nodes under echographic guidance. If the patient’s anatomical conditions do not allow it (eg, small lymph nodes), the vaccine will be distributed in more nodes (max. 500 µL/node).

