### Primary outcome measures

#### Safety

To evaluate the safety of administered tolDC, occurrence of AE will be recorded using clinical outcome measures, that is, physical (skin, pain and adenopathies) and neurological examination (relapses and worsening disability) and non-clinical outcome measures, that is, brain MRI, biochemical and haematological safety. The frequent MRI monitoring will allow us to monitor the safety of tolDC in MS patients objectively by measuring T1-enhancing lesions and new and/or enlarging T2 lesions. In this way, unexpected disease activity can be detected timely. The severity of AE will be defined according to the WHO toxicity grading scale. The relationship of an AE to the investigational product will be determined by the neurologists and the independent DSMB on the basis of their clinical judgement.

A proportion of the patients may experience MS relapses during the study. A relapse is defined as a new or worsening neurological symptom that occurs in the absence of fever or infection, occurs at least 30 days following the onset of a previous relapse, persists for at least 24 hours and includes an increase in Expanded Disability Status Scale (EDSS) score^42^ from the previous assessment matching one of the following: (i) an increase of ≥1 on the total scale score; or (ii) an increase of ≥2 points on one of the appropriate Functional System Scores (FSS) or (iii) an increase of >1 point on two or more of the appropriate FSS. Patients will be instructed to notify their neurologist as soon as possible but within 72 hours the latest and will be examined within 7 days of onset of the symptoms. In case of an MS relapse, a course of high-dose steroids can be administered at the discretion of the treating neurologist.

Study treatment must be discontinued for a given patient if the investigator determines that continuing would result in a significant risk for that patient. In case of terminating the study treatment, patients will still be monitored for safety issues for the duration of the study.

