### Analysis

Given the design of the study (phase I) and its specific primary end point (safety), no confirmatory statistical testing will be performed. P-values will be calculated but interpreted with caution. Study investigations will be exploratory and conclusions will be based on the complete set of patient evidence.

Analyses of safety variables will be performed with the safety population (all the patients treated with at least one dose of the cell product) by available data only analysis. For demographic and safety analysis, that is, the incidence of AE, laboratory values and changes in vital signs, descriptive statistics will be calculated including frequencies for categorical variables and mean and SD, or median and IQR for quantitative parameters. In brief, EDSS and other repeatedly measured variables will be analysed by means of Mixed Models for Repeated Measurements. In case model assumptions are violated (eg, non-Gaussian errors) or when dealing with ordinal efficacy variables, alternative methods (including non-parametric methods and ordinal regression methods for repeated measurements) will be used. The percentage of patients with 1-point in EDSS improvement will be estimated using a binomial regression model including the treatment and the baseline EDSS. The remainder of variables will be analysed according to the appropriate statistical test: χ^2^ or Fisher’s exact test to compare categorical variables, the dependent or independent t-test for continuous Gaussian-distributed variables and the Wilcoxon or Mann-Whitney test for ordinal and non-Gaussian continuous data. The significance level alpha will be set at 0.05 for two-tailed analysis. Variables to assess the analysis of secondary and tertiary outcome measures will be performed with per protocol population. Continuous variables as a minimum will be described by number of total and non-missing observations (n) and the appropriate location-scale statistics including arithmetic mean, SD, minimum, median, Q1–Q3 and maximum. Categorical variables will be presented using the number of non-missing observations (n) or the number of patients in the population (N) as applicable and percentages (%). Two-sided 95% (exact) CI will be provided when relevant.

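### MRI measure (ii) compares raw new or enlarging T2 lesion counts across unequal scan gaps, so follow-up counts are expected to be about 3 to 6.5 times the pretreatment count with no change in disease

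*Protocol article*

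**What the plan says.** The section MRI acquisition and evaluation sets the contrast: "Disease activity or progression on MRI will be evaluated by pretreatment versus ongoing and post-treatment". The second of its four measures is "ii) change in number of T1 Gd-enhancing and/or new or enlarging T2 lesions". This is a number of lesions. No unit of time is attached to it, and the earlier scan against which a T2 lesion counts as new or enlarging is not named.

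The Safety section under Primary outcome measures uses the same quantities to detect unexpected disease activity, "by measuring T1-enhancing lesions and new and/or enlarging T2 lesions".

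The MRI row of Table 4 places scans at Ts, T0, V1, V2, one week after each of V4, V5 and V6, and at F3, F6 and F12. The Figure 1 caption gives the timing of the visits: "Treatment will start at V_1_, approximately 4 weeks after the leukapheresis" and, for follow-up, "Patients will have follow up visits one month, and 3, 6 and 12 months following the last study treatment".

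The only reference scan described anywhere is in the eligibility criteria of Table 2: "at least one new or enlarging T2 lesion in comparison with a reference scan from maximum 1 year before".

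The Analysis section assigns repeatedly measured variables to mixed models. It allows alternative methods where assumptions fail, and lists standard tests for the remaining variables, such as "the dependent or independent t-test for continuous Gaussian-distributed variables". None of these is said to take account of the time between scans.

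**The concern.** A Gd-enhancing lesion is seen on a single scan. A new or enlarging T2 lesion is defined only by comparison with an earlier scan, so at any constant rate of lesion formation its expected number is proportional to the time between the two scans. If that time differs between the pretreatment, treatment and follow-up periods, a change in the raw number mixes a change in disease activity with a change in scan spacing.

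These are open-label trials without a control group, so the before, during and after contrast is the main internal evidence on MRI activity. An artefact in that contrast cannot be removed by comparison with a concurrent arm. The same counts are also read for safety, where a rise after the injections stop would naturally be taken as rebound or as loss of effect.

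**Working it through.** **Inputs.** Injection weeks from the Figure 1 caption are V1 = 0, V2 = 2, V4 = 6, V5 = 10 and V6 = 14. T0 (leukapheresis) is about week −4. F3, F6 and F12 are 3, 6 and 12 months after V6. With calendar months (13 weeks per quarter) they fall at 14 + 13 = 27, 14 + 26 = 40 and 14 + 52 = 66 weeks. The scans after V4, V5 and V6 are one week later, at weeks 7, 11 and 15. The timing of Ts is not given, so the Ts–T0 gap cannot be computed. The plan states no lesion rate and no figure of its own to reproduce.

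**Each scan compared with the one before.** Expected T2 count = rate × gap. The ratio to the T0–V1 count is therefore gap ÷ 4 and does not depend on the rate.

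| Scan pair | Gap (weeks) | Ratio to T0–V1 | Expected count at 1 / 2 / 5 lesions per year |
|---|---|---|---|
| T0 to V1 | 0 − (−4) = 4 | 1 | 0.08 / 0.15 / 0.38 |
| V1 to V2 | 2 − 0 = 2 | 0.5 | 0.04 / 0.08 / 0.19 |
| V2 to V4+1w | 7 − 2 = 5 | 1.25 | 0.10 / 0.19 / 0.48 |
| V4+1w to V5+1w | 11 − 7 = 4 | 1 | 0.08 / 0.15 / 0.38 |
| V5+1w to V6+1w | 15 − 11 = 4 | 1 | 0.08 / 0.15 / 0.38 |
| V6+1w to F3 | 27 − 15 = 12 | 3 | 0.23 / 0.46 / 1.15 |
| F3 to F6 | 40 − 27 = 13 | 3.25 | 0.25 / 0.50 / 1.25 |
| F6 to F12 | 66 − 40 = 26 | 6.5 | 0.50 / 1.00 / 2.50 |

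The annual rates are assumptions chosen to show a range; each count is rate × gap ÷ 52. With 4-week months the last three gaps are 11, 12 and 24 weeks, and the ratios 2.75, 3 and 6.

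**V1 as a fixed reference.** Time since V1 is then 2, 7, 11, 15, 27, 40 and 66 weeks. The cumulative count rises by 66 ÷ 2 = 33-fold from V2 to F12 through elapsed time alone.

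**After conversion to a rate.** Dividing each count by its own gap gives the same expected value at every visit when activity is constant, so every ratio becomes 1.

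**Precision of the baseline.** At an assumed 2 lesions per year, the T0–V1 interval yields 2 × 4 ÷ 52 = 0.154 expected lesions per patient, which is 0.154 × 9 = 1.4 to 0.154 × 15 = 2.3 lesions in a trial of 9 to 15 patients. The range is 0.7 to 1.2 at 1 lesion per year and 3.5 to 5.8 at 5 per year.

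**The case against.** The strongest reply is that the article condenses a fuller protocol. The reference scan, annualisation and any offset may be set out there or in an analysis plan that is not shown, and the Analysis section leaves room for alternative methods. That is fair as far as the choice of model goes, and the t-test wording should not be read as assigned to lesion counts, since it covers continuous Gaussian variables. It does not remove the point. The article does define the measure as a change in number and does fix the contrast across periods. Carried out as written, the result moves with scan spacing whichever on-study scan is the reference.

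Several limits stand:

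- Only the T2 part of measure (ii) scales with the gap. Measure (i) and the Gd-enhancing part do not, so the combined count is distorted by less than the T2 ratios above.
- On-treatment gaps nearly match T0–V1, so the ongoing-versus-pretreatment comparison is only mildly affected.
- The follow-up distortion runs against the treatment, which is the cautious direction for a first safety trial. It can still mislead about rebound.
- No confirmatory testing is planned. A dose-limiting toxicity is defined through serious adverse events, not lesion counts.

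Two stronger readings are tempting. A reader might infer that the pretreatment count will be taken against the scan of up to one year earlier. A 4-week on-treatment count would then be 1 − 4 ÷ 52 = 92% lower with no effect at all, a false benefit. The document gives that scan only as an eligibility criterion and does not name it as the comparator. A reader might also quote the 13-fold ratio between F12 and V2 (26 ÷ 2). That is post-treatment against ongoing treatment, whereas the stated contrast takes pretreatment as the base, where the largest ratio is 6.5.

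**Conclusion.** The concern holds for the new or enlarging T2 component of measure (ii), chiefly in follow-up. With consecutive-scan comparison and constant activity, the expected follow-up counts are 3, 3.25 and 6.5 times the T0–V1 count (2.75, 3 and 6 with 4-week months). On-treatment counts are 0.5 to 1.25 times. With V1 as a fixed reference, the count accumulates over 2 to 66 weeks.

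The ratios assume a constant lesion rate, lesions that remain visible until the next scan, and scans at their nominal weeks. They need no assumed rate; only the illustrative counts do. Bias towards apparent benefit would require the historical eligibility scan as the pretreatment comparator, which the document does not state. The endpoint is secondary and exploratory but also informs safety. The correction should be made because it is nearly free, but the point does not undermine the trial's primary objectives.

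**What to change.** - State that new or enlarging T2 lesions are counted against the immediately preceding on-study scan.
- Report new or enlarging T2 lesions, and combined unique active lesions, per month for the pretreatment (T0–V1), treatment and follow-up periods. Show the scan interval beside each count.
- State that the count against the historical eligibility scan is not used as the pretreatment value.
- If a model is wanted, use a simple Poisson-type count model with the logarithm of the scan interval as offset. For 9 to 15 patients per trial, descriptive rates are enough; a negative binomial repeated-measures model asks too much of so few patients.

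The cost is analysis wording only: no new scans or visits, and the intervals follow from the scan dates. The remaining weakness is that a single 4-week pretreatment interval gives an imprecise baseline rate, and this should be said when the rates are reported.

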#### Immune-monitoring

To evaluate therapy-related changes in the immune cell profile, peripheral blood (10×10 mL heparin tubes) will be sampled according to the time points depicted in figure 1 and table 3, and analysed by multiparameter flow cytometry prior to, during and after vaccination. In an attempt to cover the main leucocyte subsets of peripheral blood, the following subsets and their activation status will be enumerated in whole blood samples: CD4^+^ and CD8^+^ T cell subpopulations, B cell subsets, natural killer (NK) cells, NKT cells and myeloid cells. Myelin-specific T cell reactivity will be determined before, during and after completion of administration of tolDC. For this, responsiveness of T cells to myelin antigens will be investigated. As a control, the responsiveness of T cells to unrelated antigens, for example, cytomegalovirus or tetanus toxoid, will be addressed. In doing so, we will be able to assess ex vivo the potential risk of inducing opportunistic infections by administering tolDC to MS patients. Finally, patient materials from the studies will be specifically biobanked. We envisage to maximally performing batch measurements and centralised immune monitoring analysis as soon as a dose cohort has reached 3 months follow-up of all patients. For this, extensive immune cell profiling as well as cytokine production of T cells will be analysed by multiparameter flow cytometry. Using lineage-specific as well as activation markers, proportions and activation status of the different immune cell subsets will be determined. Besides, antibody titers and memory B cell analysis will be performed.

### Patient reported outcome measurements

MS QOL-54^37^ will be evaluated to detect changes in general and disease-specific quality of life.

### Data management and monitoring

Adequate and accurate patient records will be kept enabling the appropriate and required documentation of the study and subsequent verification of the collected data. All data are completed in the electronic case report form for each patient enrolled in this study, including patients who did not start with the investigational treatment. A central data manager affiliated to a clinical research organisation will perform source data verification. In doing so, study compliance will be monitored, thereby assuring the protection of the rights, safety and well-being of study subjects.

### Analysis

Given the design of the study (phase I) and its specific primary end point (safety), no confirmatory statistical testing will be performed. P-values will be calculated but interpreted with caution. Study investigations will be exploratory and conclusions will be based on the complete set of patient evidence.

Analyses of safety variables will be performed with the safety population (all the patients treated with at least one dose of the cell product) by available data only analysis. For demographic and safety analysis, that is, the incidence of AE, laboratory values and changes in vital signs, descriptive statistics will be calculated including frequencies for categorical variables and mean and SD, or median and IQR for quantitative parameters. In brief, EDSS and other repeatedly measured variables will be analysed by means of Mixed Models for Repeated Measurements. In case model assumptions are violated (eg, non-Gaussian errors) or when dealing with ordinal efficacy variables, alternative methods (including non-parametric methods and ordinal regression methods for repeated measurements) will be used. The percentage of patients with 1-point in EDSS improvement will be estimated using a binomial regression model including the treatment and the baseline EDSS. The remainder of variables will be analysed according to the appropriate statistical test: χ^2^ or Fisher’s exact test to compare categorical variables, the dependent or independent t-test for continuous Gaussian-distributed variables and the Wilcoxon or Mann-Whitney test for ordinal and non-Gaussian continuous data. The significance level alpha will be set at 0.05 for two-tailed analysis. Variables to assess the analysis of secondary and tertiary outcome measures will be performed with per protocol population. Continuous variables as a minimum will be described by number of total and non-missing observations (n) and the appropriate location-scale statistics including arithmetic mean, SD, minimum, median, Q1–Q3 and maximum. Categorical variables will be presented using the number of non-missing observations (n) or the number of patients in the population (N) as applicable and percentages (%). Two-sided 95% (exact) CI will be provided when relevant.

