#### Primary objectives

To evaluate the safety of administering tolDC, the occurrence and severity of adverse events (AE) will be recorded. To assess feasibility, successful production of tolDC according to good manufacturing practices (GMP) starting from a leukapheresis procedure will be assessed.

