### Study medication

Generation of tolDC will be carried out according to the principles and guidelines of GMP laid down in Directive 2003/94/EC. TolDC production will be performed in the GMP facilities of the Center for Cell Therapy and Regenerative Medicine of the Antwerp University Hospital (Belgium) and of the Cell Therapy Area of the Clínica Universidad de Navarra (Spain).

Clinical-grade autologous tolDC will be prepared from a leukapheresis. CD14^+^ monocytes will be cultured in GMP-grade cell culture medium supplemented with 2% human AB serum, granulocyte macrophage colony-stimulating factor, interleukin (IL)−4 and 1α,25 dihydroxyvitamin D_3_. At day 4, tolDC will be stimulated using an inflammatory cytokine cocktail, consisting of tumour necrosis factor-α, prostaglandin E_2_ and IL-1β. At day 6, tolDC will be harvested, loaded with seven myelin antigens (MBP_13-32_, MBP_111-129_, MBP_154-170_, PLP_139-154_, MOG_1-20_, MOG_35-55_ and MBP_83-99_), and cryopreserved at −196°C. Separate aliquots of the cell product will be prepared for quality control and quality assurance. This includes (i) sterility testing, (ii) cell count, (iii) viability, (iv) flow cytometric phenotyping and (v) induction of T cell hyporesponsiveness in an allogeneic mixed leucocyte reaction.

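### The safety population requires at least one cell dose, so adverse events of the trial leukapheresis in patients who are never injected are collected but enter no stated safety analysis

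*Protocol article*

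**What the plan says.** **Safety population.** The Analysis section of the protocol article reads: "Analyses of safety variables will be performed with the safety population (all the patients treated with at least one dose of the cell product". It then says what this covers: "For demographic and safety analysis, that is, the incidence of AE, laboratory values and changes in vital signs, descriptive statistics will be calculated". For secondary and tertiary outcomes it names the per protocol population. It defines no set of enrolled or leukapheresed patients.

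**Objectives.** Under Primary objectives, safety is worded as "To evaluate the safety of administering tolDC, the occurrence and severity of adverse events (AE) will be recorded". Feasibility, the other primary objective, begins earlier: "successful production of tolDC according to good manufacturing practices (GMP) starting from a leukapheresis procedure will be assessed". The Feasibility section adds: "This includes the production of sufficient numbers of tolDC and compliance of the final investigational product to the prespecified release criteria following cryopreservation".

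**Leukapheresis.** Under Study medication: "Clinical-grade autologous tolDC will be prepared from a leukapheresis". The legend of Figure 1 places V1 roughly 4 weeks after it.

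**Data collection.** Table 4 marks the recording of adverse and serious adverse events as continuous. It also schedules vital signs, ECG and safety bloods at T0, the leukapheresis visit. Data management and monitoring says that the case report form is completed for every enrolled patient, "including patients who did not start with the investigational treatment".

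**The concern.** Leukapheresis is performed to make the investigational product, so any harm from it is harm from taking part in the trial. A patient is exposed to it about 4 weeks before being able to enter the safety population, and the plan itself foresees that some batches may not succeed. Followed as written, the Analysis section leaves a never-injected patient's adverse events out of every stated safety summary, while the same patient counts in the feasibility result.

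At stake is whether a reader of the results can see harm from the collection procedure in all who underwent it. With 9 to 15 evaluable patients per trial, one serious event is a visible part of the safety picture. The results are also meant to inform phase II trials of a treatment that nobody can receive without this procedure.

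**Working it through.** **1. Follow a never-injected patient through the plan.**

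| Step | Where stated | Is the patient included? |
|---|---|---|
| Leukapheresis at T0 | Study medication; Table 4 | Yes |
| Adverse events recorded | Table 4 (continuous) | Yes |
| Case report form completed | Data management and monitoring | Yes |
| Production success or failure | Primary objectives; Feasibility | Yes, primary outcome |
| Incidence of adverse events, laboratory values, vital signs | Analysis | No, needs at least one dose |
| Any other stated safety set | None found | No |

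The gap therefore lies in the analysis and not in data collection. The Analysis section also says that conclusions will rest on all the patient evidence, but that sentence names no population and no summary, so it does not fill the gap.

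**2. Reproduce the plan's own figure.** Table 3 gives three cohorts of 3 (+1+1) patients: 3 × 3 = 9 to 3 × 5 = 15, which matches the stated 9–15 evaluable patients per trial. Evaluable is taken below to mean injected (assumption).

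**3. Scale.** The document gives no rate f of leukapheresed patients who are never injected, so f is assumed, from 5% to 30%.

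- Expected leukaphereses for n injected patients: n/(1 − f). Expected never injected: n/(1 − f) − n.
- Chance of at least one never-injected patient before the n-th injected one: 1 − (1 − f)^n.

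| f (assumed) | n = 9: expected never injected | n = 9: chance of at least one | n = 15: expected never injected | n = 15: chance of at least one |
|---|---|---|---|---|
| 5% | 0.47 | 37% | 0.79 | 54% |
| 10% | 1.00 | 61% | 1.67 | 79% |
| 20% | 2.25 | 87% | 3.75 | 96.5% |
| 30% | 3.86 | 96% | 6.43 | 99.5% |

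**4. One serious event in a never-injected patient (also assumed), f = 10%.** Leukaphereses: 9/0.90 = 10, and 15/0.90 = 16.7, rounded up to 17. Exact (Clopper-Pearson) 95% intervals; the upper limit for 0/n is 1 − 0.025^(1/n) and the lower limit for 1/m is 1 − 0.975^(1/m).

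| Injected patients | Safety population as planned | All leukapheresed |
|---|---|---|
| 9 | 0/9 = 0% (0 to 33.6%) | 1/10 = 10.0% (0.25 to 44.5%) |
| 15 | 0/15 = 0% (0 to 21.8%) | 1/17 = 5.9% (0.15 to 28.7%) |

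The intervals overlap almost entirely, so this is no contrast between two rates. It shows that a serious event that occurred would be absent from the safety table.

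**The case against.** **The population fits the objective.** The safety question is put throughout as the safety of administering tolDC, and patients with at least one dose are the ordinary set for it. The sentence that starts from leukapheresis belongs to feasibility. This stands: the at-least-one-dose set should be kept, and the point concerns only what lies outside it.

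**The patients are not invisible.** Production failure is a primary outcome and the events are on the case report form. This also stands. It would be wrong to say that these patients yield no safety data; the data exist but have no stated place in the safety results.

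**The analysis plan may contain such a table.** It may, and then nothing remains to be done. But the article does not leave the matter open: it fixes one population for all safety variables, so the exclusion is a stated rule and not a detail left to the analysis plan.

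**Stronger readings that a reader might infer.**

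- That events before V1 in injected patients mix with later events and blur the comparison of doses and routes. The document fixes no time window for adverse events, and a split at first dose is usual content of an analysis plan. Relationship to the product is judged by the neurologists and the independent Data Safety Monitoring Board, and escalation rests on dose-limiting toxicities. Both trials begin with leukapheresis, and nothing suggests that its events differ by dose or route.
- That the loss is selective because poor yield goes with poor tolerance. Yield and release are laboratory outcomes, and nothing in the document links them to adverse events. Only withdrawal because of a leukapheresis event is a clear selective route.

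**Conclusion.** The point holds in limited form. Under the stated rule, leukapheresis events in patients who are never injected are collected but belong to no stated safety analysis, although these patients count in the primary feasibility outcome. Leukapheresis events in patients who are later injected are not removed by the rule.

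The size is unknown. It depends on how many patients are never injected, which the document does not give, and on whether any of them has an event. The 0/9 against 1/10 and 0/15 against 1/17 figures rest on an assumed 10% non-injection rate and one assumed serious event.

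A reader might conclude that the reported safety will be too favourable. The document supports that only as a possibility, not as a demonstrated bias. The dose-escalation rule, the sample size and the choice of treated set for product safety are not in question. This is a gap in reporting that is cheap to close.

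**What to change.** Keep the at-least-one-dose population for the safety of the cell product. Add to the Analysis section a second descriptive set, all patients who start leukapheresis, and summarise in it the adverse and serious adverse events from the start of leukapheresis to V1, or to withdrawal for those never injected. State how many of the set were never injected and why (too few cells, failed release, withdrawal), so that the table lines up with the feasibility result.

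Cost: one sentence on the population and one extra table for each trial. The data are already planned, and no visit, patient, test or escalation decision changes.
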